#### 7.3.1 Primary analysis

Paired t-tests will be performed to test the difference in the GFR response between baseline and after treatment of BI 10773 (25 mg QD) in hyperfilterer subjects under separate

Proprietary confidential information.

© 2012 Boehringer Ingelheim International GmbH or one or more of its affiliated companies. All rights reserved.

This document may not - in full or in part - be passed on, reproduced, published or otherwise used without prior written permission.

conditions of controlled euglycaemia and hyperglycaemia. The primary analysis will be performed on the FAS\_RENAL.

### 7.3.2 Secondary analyses

#### 7.3.2.1 Secondary analyses

The secondary analyses will focus on additional between-group and within-group comparisons of the primary endpoint. The analyses will be performed on the FAS\_RENAL.

Since the hyperfilterer and non-hyperfilterer subjects were not randomized into the trial, the two groups may not be comparable. Thus, caution should be used interpreting the results of the between-group analyses.

#### Within group comparisons:

Paired t-tests will be performed to test the difference in the GFR response between baseline and after treatment of BI 10773 (25 mg QD) in non-hyperfilterer subjects under separate conditions of controlled euglycaemia and hyperglycaemia.

Paired t-tests will be performed to test the difference in the GFR response between baseline and after treatment of BI 10773 (25 mg QD) in all subjects under separate conditions of controlled euglycaemia and hyperglycaemia.

#### Between-group comparisons (hyperfilterer vs non-hyperfilterer):

Analysis of covariance (ANCOVA) will be performed on the primary endpoint to assess the difference between hyperfilterer versus non-hyperfilterer subjects under separate conditions of controlled euglycaemia and hyperglycaemia.

The model will include the baseline GFR and group (i.e., hyperfilterer vs. non-hyperfilterer) as independent parameters. In the event of significant results for the group covariate, adjusted means will be reported. It is hypothesized that there is a difference in the mean change of the GFR between the hyperfilterer subjects and non-hyperfilterer subjects.

In addition, the interaction of the primary endpoint will be assessed as a sensitivity analysis.

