## 7. STATISTICAL METHODS AND DETERMINATION OF SAMPLE SIZE

### 7.1 STATISTICAL DESIGN - MODEL

This is an open-label, single centre pilot study to characterize: 1) the impact of BI 10773 on renal hyperfiltration in subjects with T1DM under conditions of controlled euglycaemia and hyperglycaemia and 2) the safety and efficacy of BI 10773-treatment as adjunctive-to-insulin therapy in these subjects.

Subjects who successfully complete the open-label placebo run-in period and meet the inclusion/exclusion criteria will be entered in the study and receive BI 10773 25 mg QD for 8 weeks. The subjects will be stratified into 2 groups based on their baseline GFR measured under a clamped euglycaemia condition at Visit 3 assessed by inulin measurements. The non-hyperfilterers will be subjects with a measured GFR of  $\geq 60$  ml/min/1.73m^2 to  $< 135$  ml/min/1.73m^2 and hyperfilterers will be subjects with a measured GFR  $\geq 135$  ml/min/1.73m^2.

Table 7.1: 1 below describes the population, clamped condition, baseline and treatment assessments. Renal data (e.g., GFR) will be collected on days 1, 2, 57 and 58 for Hyperfilterer and Non-Hyperfilterer subjects.

Table 7.1: 1 Summary of populations, clamped conditions, baseline and treatment assessments

|                    | Baseline                 |                | After 8 weeks of treatment with BI 10773 |                |
|--------------------|--------------------------|----------------|------------------------------------------|----------------|
| Population  | Clamped Condition |                | Clamped Condition                 |                |
|                    | Day 1             | Day 2   | Day 57                            | Day 58  |
| Hyperfilterers     | Euglycaemia              | Hyperglycaemia | Euglycaemia                              | Hyperglycaemia |
| Non-Hyperfilterers |                          |                |                                          |                |

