### **7.6 DETERMINATION OF SAMPLE SIZE**

For this trial, between-group analysis and within-group analysis will be performed. The sample size calculations are based on the between-group analysis. Listed below in [Table 7.6: 1](#) are the sample size calculations based on a two-group t-test (two-sided,  $\alpha=0.05$ ), which looks at the difference between the hyperfilterer and non-hyperfilterer groups.

With the sample size of 12 subjects per group and assuming that the standard deviation is 5, a two-group t-test with a 0.05 two-sided significance level will have 80% power to detect a difference in the means of 6 (i.e., the difference between group 1 (Hyperfilterer) mean and Group 2 (Non-hyperfilterer) mean). If the standard deviation is increased to 6, a sample size of 17 subjects per group would be required. As such, a minimum of 12 subjects per group will need to complete the trial (Visit 13) and therefore approximately 30 subjects will need to be entered to achieve the sample size requirements.

Proprietary confidential information.

© 2012 Boehringer Ingelheim International GmbH or one or more of its affiliated companies. All rights reserved.

This document may not - in full or in part - be passed on, reproduced, published or otherwise used without prior written permission.

Table 7.6: 1 Sample size calculations based on a two-group t-test (two-sided,  $\alpha=0.05$ )

| Mean Change
for
Hyperfilterer
Group | Mean Change
for Non-
hyperfilterer
Group | Difference
between the
groups | Standard
Deviation | Power
(%) | N
per group |
|----------------------------------------------|---------------------------------------------------|-------------------------------------|-----------------------|--------------|----------------|
| 8                                            | 5                                                 | 3                                   | 3.5                   | 80           | 23             |
| 8                                            | 5                                                 | 3                                   | 5                     | 80           | 45             |
| 8                                            | 5                                                 | 3                                   | 6                     | 80           | 64             |

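### The 80% power in Section 7.6 belongs to an unadjusted two-group t-test that is not planned; the planned ANCOVA estimates something else under euglycaemia and probably has less power under both clamps

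*Protocol*

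**What the plan says.** Section 7.6 of the protocol: "The sample size calculations are based on the between-group analysis". Taking an SD of 5 and 12 completers in each arm of the comparison, it claims that "a two-group t-test with a 0.05 two-sided significance level will have 80% power to detect a difference in the means of 6". It adds that "If the standard deviation is increased to 6, a sample size of 17 subjects per group would be required". Section 5.2.3 repeats the t-test rationale, and the minimum of 12 completers per group governs recruitment (3.2), the end of screening (3.3) and replacement of early discontinuations (3.3.4.1).

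The planned analyses are different. The primary analysis (7.3.1) is paired t-tests in hyperfilterers. The between-group analysis (7.3.2.1) reads: "Analysis of covariance (ANCOVA) will be performed on the primary endpoint to assess the difference between hyperfilterer versus non-hyperfilterer subjects", separately under each clamp. Its terms are fixed as well: "The model will include the baseline GFR and group (i.e., hyperfilterer vs. non-hyperfilterer) as independent parameters". The hypothesis given there is a difference between the groups in mean change of GFR.

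Groups are formed in Section 7.1: "The subjects will be stratified into 2 groups based on their baseline GFR measured under a clamped euglycaemia condition at Visit 3", with the cut at 135 ml/min/1.73m². The baseline definitions in the same section make Visit 3 the renal baseline for Visit 12 (euglycaemia) and Visit 4 the renal baseline for Visit 13 (hyperglycaemia).

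**The concern.** The test that justifies the sample size is not among the planned analyses, and the one that takes its place targets a different quantity. In the euglycaemia ANCOVA, group is fully determined by the covariate: every subject at or above 135 is in one group and everyone below is in the other. There is no range of baseline GFR in which both groups occur. The group coefficient is therefore the jump in change at 135, obtained by extrapolating a common slope from both sides. The hypothesis in 7.3.2.1 and the sizing in 7.6 concern the difference in mean change (11 versus 5). If the GFR fall simply grows with baseline GFR, the covariate absorbs that difference.

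At stake is interpretation. A non-significant euglycaemic group term could be read as an equal response in the two groups, with an 80% power statement apparently behind it. Adjusted means, which 7.3.2.1 reports only after a significant group term, would be evaluated at a baseline value that at least one group cannot contain.

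**Working it through.** **Inputs from the protocol.** n = 12 per group; difference in mean change 6; SD 5; two-sided alpha 0.05 (7.6). ANCOVA terms: baseline GFR and group (7.3.2.1). Cut at 135 on Visit 3 GFR (7.1). The protocol gives neither a distribution of baseline GFR nor a correlation of baseline with change; both are assumed below.

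**1. The stated figure.** Noncentral t with 22 df and noncentrality 6 / (5 × √(2/12)) = 2.94 gives 80.2% power. All ten rows of Table 7.6: 1 reproduce exactly.

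**2. Euglycaemia ANCOVA, step of 6, residual SD 5.** The variance of the group effect is multiplied by VIF = 1/(1 − R²), where R² is the squared correlation of group with baseline GFR; residual df are 21. For a normal baseline split at its median, R² = 2/π = 0.64 and VIF = 2.75. Noncentrality is 2.94/√2.75 = 1.77, and power is 39%. In simulated samples of 12 + 12 the mean VIF is about 3.1 and power is 37%.

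| Assumed baseline GFR | Power of group term |
|---|---|
| Normal, split at median | 37–39% |
| Truncated normal, cut at 135 (several means and SDs) | 35–36% |
| Uniform on either side of the cut | 28–29% |
| Two well-separated clusters (115 and 160, SD 10) | 19% |
| R² set at 0.5 / 0.8 | 51% / 24% |

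At R² = 0.64, about 32 per group would be needed for 80%.

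**3. If baseline explains part of the SD of 5.** Residual SD = 5 × √(1 − ρ²), where ρ is the within-group correlation of baseline with change. With VIF 2.75: ρ = 0.5 gives 4.33 and 50% power; ρ = 0.7 gives 3.57 and 66%; ρ = 0.8 gives 3.00 and 80%. These figures still assume a true step of 6.

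**4. If the difference of 6 comes wholly from a linear slope.** With a normal baseline split at its median, the group means of baseline lie 2 × √(2/π) = 1.596 SD apart, so the slope is 6/1.596 = 3.76 per SD. Within-group baseline variance is 1 − 2/π = 0.363 in squared SD units. To keep the within-group SD of change at 5, the residual SD is √(25 − 3.76² × 0.363) = 4.46. In simulation the t-test rejects in 79.5% of trials and the ANCOVA group term in 4.6%, which is the alpha level.

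**5. Hyperglycaemia ANCOVA.** The covariate is Visit 4 GFR, so R² = r² × 0.637, with r the assumed Visit 3/Visit 4 correlation. For r = 0.7, VIF = 1/(1 − 0.312) = 1.45 and power is 64%. For r = 0.9, the large-sample VIF is 1/(1 − 0.516) = 2.06 (power 50%); the mean VIF in samples of this size is about 2.3 (power 46%).

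**6. The primary test.** Paired t-test, 12 hyperfilterers, one-sided 0.025, 11 df. Power of 80% is reached at a fall of 4.4 (SD 5) or 7.1 (SD 8). For the hyperfilterer falls in Table 7.6: 1 (8 to 11), power is at least 88% for SD 5 to 8, taking the table's SDs as SDs of the paired change.

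**The case against.** The other side has four good arguments.

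- **The ANCOVA's power cannot be computed from the protocol.** A reader might infer that it is about 36% on the plan's own numbers. The documents do not support that: the figure needs a baseline distribution, an adjusted effect that stays at 6 and a residual SD that stays at 5. The objection stands, so power is given here only as a range tied to those assumptions.
- **The exact overlap is confined to euglycaemia.** It would be too strong to say that the model cannot compare the groups at all. Under hyperglycaemia Visit 4 GFR does not define the group, and the loss of power is smaller. This also stands.
- **The primary analysis is sound.** The absence of a power figure for it might suggest that the primary test is weak. It is not: the detectable falls of 4.4 and 7.1 lie below every hyperfilterer change in Table 7.6: 1. The ANCOVA is a secondary analysis in a study that 7.2 calls exploratory. Section 7.3.2.1 already urges caution with between-group results, though because of non-randomisation and not this overlap. Both within-group changes will be shown as well.
- **The unadjusted t-test has its own bias under euglycaemia.** Groups are selected on the same Visit 3 value that is subtracted to form the change. Assume a baseline SD of 20 split at 135 and a slope of follow-up on baseline of 0.9. The group baselines then differ by 2 × 20 × 0.798 = 31.9, and regression to the mean alone yields a difference of 0.1 × 31.9 = 3.2. At an SD of change of 5 the t-test would reject about 31–32% of the time with no true group difference. Replacing the ANCOVA by that test as the main euglycaemic analysis is therefore a trade-off, not a clean repair.

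None of this removes the mismatch between 7.6 and 7.3.2.1, or the change in what the group term estimates.

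**Conclusion.** The point holds, within limits. Two parts rest on the protocol's text alone: the 80% describes a test that is not planned, and the euglycaemia group coefficient is not the difference in mean change that 7.3.2.1 hypothesises and 7.6 sizes.

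The size of the power loss rests on assumptions. Under euglycaemia it is about 35–39% for a normal-type baseline cut near its centre, with adjusted effect 6 and residual SD 5. It is about 19–51% over the other baseline shapes tried, 50–80% if baseline correlates 0.5–0.8 with change within group, and about 5% if change is purely linear in baseline. Under hyperglycaemia it is about 46–64% for Visit 3/Visit 4 correlations of 0.9 down to 0.7.

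A reader should not conclude that the trial is underpowered for its primary question. Severity is should-fix: the fault lies in a secondary analysis of an exploratory pilot, but it is the comparison on which the sample size was built.

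**What to change.** **Section 7.6.**
- State that the 80% applies only to the unadjusted difference in mean change, not to the planned ANCOVA.
- Give the ANCOVA's power as a range, with its assumptions on baseline distribution, adjusted effect and residual SD.
- Add the figure for the actual primary test: 12 hyperfilterers, one-sided 0.025, 80% power for a fall of 4.4 at SD 5 or 7.1 at SD 8.

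**Section 7.3.2.1.**
- State that the euglycaemia group coefficient is not to be read as the difference in mean change.
- Report the unadjusted difference in mean change with a 95% confidence interval under both clamps, labelled descriptive under euglycaemia because of regression to the mean.
- Add a supportive regression of change on continuous baseline GFR in all subjects, without the group term. Change and baseline share the Visit 3 value under euglycaemia, and the Visit 4 value under hyperglycaemia, so the same caution applies.

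There is no need to name one clamp as the main condition; the protocol treats them in parallel.

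**Cost.** Wording only; no extra subjects or data. The stated power for the between-group analysis becomes less favourable, and the euglycaemic contrast becomes descriptive.

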#### 7.3.2.2 Other analyses

#### Other exploratory renal analyses

For the other exploratory renal endpoints, between-group and within-group comparisons will be performed. The analysis will be performed on the FAS\_RENAL.

#### Within group comparisons:

Paired t-tests will be performed to test the difference in the response between baseline and after treatment of BI 10773 (25 mg QD) in hyperfilterer subjects under separate conditions of controlled euglycaemia and hyperglycaemia.

Proprietary confidential information.

© 2012 Boehringer Ingelheim International GmbH or one or more of its affiliated companies. All rights reserved.

This document may not - in full or in part - be passed on, reproduced, published or otherwise used without prior written permission.

Paired t-tests will be performed to test the difference in the response between baseline and after treatment of BI 10773 (25 mg QD) in non-hyperfilterer subjects under separate conditions of controlled euglycaemia and hyperglycaemia.

Paired t-tests will be performed to test the difference in the response between baseline and after treatment of BI 10773 (25 mg QD) in all subjects under separate conditions of controlled euglycaemia and hyperglycaemia.

The following analyses will be performed:

- Difference in the renal hemodynamic function (ERPF, RBF, FF, RVR) response between baseline and after treatment of BI 10773 (25 mg QD).
- Difference in the systemic hemodynamic function (MAP and arterial stiffness) response between baseline and after treatment of BI 10773 (25 mg QD).
- Difference in the circulating levels of mediators involved in RAAS activation and markers of sympathetic activity response between baseline and after treatment of BI 10773 (25 mg QD).
- Difference in the markers of glomerular and tubular integrity (nitric oxide, prostanoids and albumin excretion) response between baseline and after treatment of BI 10773 (25 mg QD).

Between-group comparisons (hyperfilterer vs non-hyperfilterer):

Analysis of covariance (ANCOVA) will be performed on the exploratory renal endpoints to assess the difference between hyperfilterer versus non-hyperfilterer subjects under separate conditions of controlled euglycaemia and hyperglycaemia.

The model will include the renal endpoint at baseline and group (i.e., hyperfilterer vs. non-hyperfilterer) as independent parameters. In the event of significant results for the group covariate, adjusted means will be reported. It is hypothesized that there is a difference in the mean change of the renal endpoint between the hyperfilterer subjects and non-hyperfilterer subjects.

Other exploratory diabetes analyses

Descriptive statistics will be used to summarize and evaluate the other diabetes-related endpoints. In addition, analyses will be performed to evaluate the follow-up period (Visits 14 and 15). These analyses will be performed on the FAS\_T1DM.

Proprietary confidential information.

© 2012 Boehringer Ingelheim International GmbH or one or more of its affiliated companies. All rights reserved.

This document may not - in full or in part - be passed on, reproduced, published or otherwise used without prior written permission.

Definition of responder for HbA1c, hypoglycaemia and insulin requirements:

Responder classification will be performed based on the change in HbA1c, hypoglycaemia and insulin requirements from baseline. The responder criterion will be defined as a composite of the following parameters:

- HbA1c change:
  - Improvement: Defined as  $\geq 0.3\%$  lowering relative to baseline
  - No change: Defined  $< 0.3\%$  lowering to  $> 0.3\%$  increase relative to baseline
  - Worsening: Defined as  $\geq 0.3\%$  increase relative to baseline
- Hypoglycaemia change:
  - Improvement: Defined as 30% lowering relative to baseline
  - No change: Defined  $< 30\%$  lowering to  $> 30\%$  increase relative to baseline
  - Worsening: Defined as  $\geq 30\%$  increase relative to baseline
- Insulin requirement change:
  - Improvement: Defined as 20% lowering relative to baseline
  - No change: Defined  $< 20\%$  lowering to  $> 20\%$  increase relative to baseline
  - Worsening: Defined as  $\geq 20\%$  increase relative to baseline

Details of responder classification are provided below (Figure 7.3.2.2: 1):

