##### Visit 4 (Day 2, Non-Fasted):

- Renal panel (clamped hyperglycaemia condition)

For symptomatic hypoglycaemic events the pre-treatment period is defined as the 2 week run-in period. For time spent in CGM-defined hypoglycaemia, the pre-treatment period is defined as the 2 week of CGM assessment during the run-in phase. Visit 3 renal measurements and Visit 4 renal measurements are respectively baseline measurements for Visit 12 and 13.

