| Response:           | [figure not shown]  | [figure not shown] | [figure not shown] | [figure not shown] | [figure not shown] | [figure not shown] | [figure not shown] | [figure not shown] | [figure not shown] | [figure not shown] |

Per the above classification, a responder (X) is defined as a subject with:

- An improved HbA1c and an improved or unchanged hypoglycaemia, irrespective of insulin changes
- An unchanged HbA1c with an improved hypoglycaemia, irrespective of insulin changes
- An unchanged HbA1c and an unchanged hypoglycaemia with improved insulin requirements

Figure 7.3.2.2: 1 Summary of responder classification

Proprietary confidential information.

© 2012 Boehringer Ingelheim International GmbH or one or more of its affiliated companies. All rights reserved.

This document may not - in full or in part - be passed on, reproduced, published or otherwise used without prior written permission.

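### The responder category limits in section 7.3.2.2 overlap for increases and, for hypoglycaemia and insulin, leave larger reductions without a category

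*Protocol*

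**What the plan says.** The Synopsis and section 5.1.1 list a combined HbA1c, hypoglycaemia and insulin endpoint and send the reader to section 7.3.2 for the classification. Section 7.3.2.2 gives the limits.

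- **HbA1c:** the best category is given as "Improvement: Defined as $\geq 0.3\%$ lowering relative to baseline". The middle category is worded "No change: Defined $< 0.3\%$ lowering to $> 0.3\%$ increase relative to baseline", and the bottom category is "Worsening: Defined as $\geq 0.3\%$ increase relative to baseline".
- **Hypoglycaemia:** the best category is given as "Improvement: Defined as 30% lowering relative to baseline". The middle category is worded "No change: Defined $< 30\%$ lowering to $> 30\%$ increase relative to baseline", and the bottom category is "Worsening: Defined as $\geq 30\%$ increase relative to baseline".
- **Insulin requirement:** worded as for hypoglycaemia, with 20% in place of 30%.

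The text under Figure 7.3.2.2: 1 then makes a subject a responder in three ways:

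1. HbA1c improved and hypoglycaemia improved or unchanged, whatever happens to insulin.
2. HbA1c unchanged "with an improved hypoglycaemia, irrespective of insulin changes".
3. HbA1c and hypoglycaemia both unchanged, and insulin improved.

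These rules use only the category names. They do not restate or repair the limits.

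**The concern.** Three ordered categories should place every possible change in exactly one of them. Here the upper limit of *no change* has its inequality sign the wrong way round in all three components. The at-least sign before the improvement cut-off is present for HbA1c but absent for hypoglycaemia and insulin.

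Because the responder rules rest directly on these labels, two analysts following the text could count different responders from the same data. Reductions beyond 20% in insulin are also plausible from the design: section 4.2.1 has subjects cut basal and bolus insulin by about 30% when treatment starts, although later titration may change that. The trial is open-label with a single treatment group, so any choice between readings made late would be made with the results in view.

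**Working it through.** The protocol states no sample size, power or expected proportion for this endpoint, so there is no figure to reproduce. The check is whether the printed limits form a partition.

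**Inputs (section 7.3.2.2).** Let c be the signed change (positive means increase) and x the cut-off: 0.3 for HbA1c, 30% for hypoglycaemia, 20% for insulin. I read the HbA1c cut-off as percentage points.

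**Limits as printed**

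- Improvement: c ≤ −x for HbA1c; c = −x for hypoglycaemia and insulin.
- No change: c > −x, running on beyond +x. The text gives no finite upper end. Whatever end is assumed, it lies above x.
- Worsening: c ≥ x.

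**Classifying a grid of changes**

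| Change | HbA1c (x = 0.3) | Hypoglycaemia (x = 30%) | Insulin (x = 20%) |
|---|---|---|---|
| −2x | improvement | none (−60%) | none (−40%) |
| −1.01x | improvement | none (−30.3%) | none (−20.2%) |
| −x | improvement | improvement | improvement |
| −0.99x | no change | no change | no change |
| 0 | no change | no change | no change |
| +0.99x | no change | no change | no change |
| +x | no change and worsening | no change and worsening | no change and worsening |
| +1.01x | no change and worsening | no change and worsening | no change and worsening |
| +2x | no change and worsening | no change and worsening | no change and worsening |

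The overlap is in all three components. The gap is in hypoglycaemia and insulin only.

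**Effect on responder status.** Of 3 × 3 × 3 = 27 label combinations, 6 meet rule 1, 3 meet rule 2 and 1 meets rule 3, so 10 are responders. Worked cases:

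| HbA1c | Hypoglycaemia | Insulin | As printed | With closed limits |
|---|---|---|---|---|
| +0.5 | −30% | 0 | responder if HbA1c is read as unchanged (rule 2), non-responder if worsened | non-responder |
| −0.5 | +50% | 0 | responder if hypoglycaemia is read as unchanged (rule 1), non-responder if worsened | non-responder |
| 0 | −50% | 0 | cannot be classified | responder (rule 2) |
| 0 | 0 | −25% | cannot be classified | responder (rule 3) |

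The defects do not all matter equally. The insulin overlap never changes responder status, because no rule separates unchanged from worsened insulin. The insulin gap matters only under rule 3. The HbA1c and hypoglycaemia overlaps, and the hypoglycaemia gap, can each change the result.

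**Closed limits.** With improvement c ≤ −x, no change −x < c < x and worsening c ≥ x, every grid point falls in exactly one category for all three components.

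**The case against.** The best reply is that the intended limits are easy to infer. The labels are ordered, worsening is given its own explicit limit each time, and HbA1c improvement does carry the at-least sign. For hypoglycaemia and insulin, *no change* begins just short of the improvement cut-off, which only makes sense if improvement means that much or more. This stands, and it makes the defect a drafting error with an obvious repair. It also means that a reader should not infer that subjects with a rising HbA1c will be counted as responders: the worsening line is there, and the text is contradictory rather than permissive. It does not remove the need to correct limits that the protocol itself chose to fix. The symbols in the figure are not visible in the text available, but the written rules beneath it do not restate the limits.

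A reader might go further and infer that the hypoglycaemia component sets a raw 2-week run-in count against an 8-week treatment count, and that it breaks down for subjects with no run-in events. The documents do not support that as a finding. Section 7.1 does say "For symptomatic hypoglycaemic events the pre-treatment period is defined as the 2 week run-in period", but it also defines a run-in baseline for CGM-defined hypoglycaemia time, and section 7.3.2.2 does not name the measure used in the responder definition. CGM hypoglycaemia is expressed there as a percentage of time, and the example CGM treatment windows in section 5.3.2.2 are 2-week periods. No section proposes comparing raw counts over unequal periods, and no event rates are given from which to size a zero-baseline problem. The measure, its rate basis and the handling of a zero baseline can properly be left to the statistical analysis plan, which is not shown.

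The endpoint is also one of 14 exploratory diabetes endpoints in section 5.1.1, summarised descriptively. That limits the importance of the point, not its correctness.

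**Conclusion.** The point holds for the category limits. As printed, an increase at or above the cut-off is both no change and worsening in all three components, and a reduction beyond 30% in hypoglycaemia or 20% in insulin belongs to no category. Responder status can be ambiguous or undefined as a result.

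How many subjects would be affected cannot be stated, because the protocol gives no expected distribution for these changes. The reach is small: one exploratory, descriptive endpoint, with no hypothesis, significance level or sample size depending on it and no effect on the primary GFR analysis. The conclusion rests on the printed inequality signs. The same pattern at 0.3%, 30% and 20% makes an error in reading the PDF unlikely for the overlap.

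**What to change.** In section 7.3.2.2, restate each component with one closed set of limits:

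- Improvement: lowering of at least x.
- No change: lowering of less than x up to an increase of less than x.
- Worsening: increase of at least x.

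Here x is 0.3 percentage points for HbA1c, 30% for hypoglycaemia and 20% for insulin requirement. Check that the key and cells of Figure 7.3.2.2: 1 agree. The three responder rules can stay as they are. The cost is a wording change with no new data, best made before the responder results are tabulated. The statistical analysis plan is the natural place to name the hypoglycaemia measure, its rate basis and the treatment of a zero baseline.
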